### Outcomes and Measures

The primary endpoint of this study will be superior graft survival measured as the time to allograft loss, defined as the composite of return to dialysis, retransplant, death due to allograft failure, and DWFG (infection, malignancy, and cardiovascular death).

Secondary endpoints include assessment of allograft function and immunological status. Allograft function will be measured as the relative change in eGFR from baseline between the 2 study groups: dd-cfDNA surveillance compared to controls. Immunological status will be defined by detection of de novo DSA formation in patients monitored using dd-cfDNA compared to the matched controls.

All clinical events and investigation results will be captured through the patient electronic medical record or via AlloCare, an optional smartphone-based application that provides a patient-driven platform to manage medications, access results, monitor wellness activities, and streamline communication with their care team. Patients will also be offered mobile phlebotomy when they are unable to visit a local laboratory. The mobile blood draw will be coordinated by CareDx, which will draw all regular tests, urine samples, as well as the AlloSure. Support for testing adherence will be provided by PCMs (CareDx Inc, Brisbane, CA) to assist with scheduling both in-center and mobile draws and provide laboratory visit reminders.

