**Exclusion Criteria**
Participant who is pregnant, lactating, or planning pregnancy during the trialSignificant hepatic impairment (determined by the principal investigator)Participant with life expectancy of <6 months or inappropriate for diagnostic monitoring through regular blood sampling<6 months and >18 months posttransplantAny other significant disease or disorder which, in the opinion of the investigator, may either put the participants at risk because of participation in the trial or may influence the result of the trial or the participant’s ability to participate in the trialParticipants who have participated in another research trial involving an investigational product in the past 12 weeksRecipients of multiorgan transplant (eg, kidney-pancreas)Recipients of a transplant from a monozygotic (identical) twinRecipients of nonautologous bone marrow transplantPatients with a history of poor compliance or needle phobia

A 2-sided log-rank test with an overall sample size of 3500 kidney transplant patients (of which 2500 will be periodically assessed with AlloSure and 1000 are matched controls receiving standard of care) achieves 87% power at a 5% significance level to detect an allograft survival difference of 5% (ie, 75%, AlloSure assessed; 70%, standard of care) during the 5-year surveillance period. This corresponds to a hazard ratio of 0.807, which is a 19.3% reduction in the risk of allograft loss in the AlloSure-assessed patients in comparison to standard of care. There is no consideration of patients lost to follow-up due to the United Network for Organ Sharing U.S. Scientific Registry of Transplant Recipients database, which tracks transplanted organ survival for all organ transplant recipients; however, this analysis does account for an attrition rate of 65%.

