A decline in GFR has been shown to be a valid surrogate for long-term outcome in renal transplantation. A 2-sided *t* test or its nonparametric analog will be used to assess differences in the distribution of 5-year change from baseline in eGFR between AlloSure and standard of care surveillance groups. These tests will have approximately 76% power at a 5% significance level to detect a 25% difference in eGFR decline over the 5-year surveillance period. This assumes, over the 5-year surveillance period, an average of 12 mL/min per 1.73 m^2^ decline in eGFR for standard of care and an average 9 mL/min per 1.73 m^2^ decline in eGFR for AlloSure (both groups having similar standard deviations of 30 mL/min per 1.73 m^2^).

Assuming the proportion of control subjects with formation of de novo DSA antibodies during the 5-year surveillance period is 40%, a 2-sided Z-test with continuity correction and pooled variance with the aforementioned sample size of 3500 achieves 78% power at a 5% significance level to detect a de novo DSA formation difference of 5% (ie, 35%, AlloSure assessed; 40%, standard of care) during the 5-year study surveillance period.

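### The 76% power for the 5-year eGFR change counts all 3500 patients, although the same section expects 25% and 30% to have lost the graft or died; among surviving grafts it is about 62%

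*Protocol article*

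**What the plan says.** The relevant text is in the sample size paragraphs that follow the Exclusion Criteria in Methods.

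- **Test.** The eGFR analysis looks for "differences in the distribution of 5-year change from baseline in eGFR between AlloSure and standard of care surveillance groups". The planned method is a two-sided t test, and a nonparametric counterpart is allowed in its place.
- **Power.** "These tests will have approximately 76% power at a 5% significance level to detect a 25% difference in eGFR decline". The inputs are "an average of 12 mL/min per 1.73 m^2^ decline in eGFR for standard of care" against "an average 9 mL/min per 1.73 m^2^ decline in eGFR for AlloSure", with "both groups having similar standard deviations of 30 mL/min per 1.73 m^2".
- **Expected graft survival.** The paragraph just before, on the primary endpoint, plans for 2500 AlloSure patients and 1000 matched controls, with 5-year allograft survival of "75%, AlloSure assessed; 70%, standard of care".
- **Meaning of loss.** Outcomes and Measures defines allograft loss as return to dialysis, retransplant, death from graft failure or death with a functioning graft.
- **Scale.** Outcomes and Measures also says: "Allograft function will be measured as the relative change in eGFR from baseline between the 2 study groups". The power statement works in absolute mL/min per 1.73 m2.

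**The concern.** A patient who has died, returned to dialysis or been retransplanted has no 5-year eGFR from the study graft. The plan expects this for 25% of AlloSure patients and 30% of controls, yet the eGFR paragraph makes no visible allowance for it. Two things follow if only observed 5-year changes are compared.

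1. The effective sample is smaller than the one behind the stated power.
2. The groups compared are selected on graft survival, which the intervention is meant to improve. The eGFR paragraph itself treats GFR decline as a surrogate for long-term outcome, so the plan's own premise links loss and decline. A difference among survivors is then not a clean comparison of the two cohorts.

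At stake are the credibility of one secondary endpoint's power statement and the interpretation of its result. The primary endpoint is not affected.

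**Working it through.** **Inputs, all from the sample size paragraphs:** difference 12 − 9 = 3 mL/min per 1.73 m2; SD 30 in both groups; two-sided 5% level (critical value 1.960); 2500 and 1000 patients; 5-year graft survival 75% and 70%.

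**Formula:** Z = difference / [SD × √(1/n₁ + 1/n₀)]; power ≈ Φ(Z − 1.960).

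**Step 1. Reproduce the stated figure.** With n₁ = 2500 and n₀ = 1000:
- √(1/2500 + 1/1000) = √0.0014 = 0.03742
- Z = 3 / (30 × 0.03742) = 2.673
- power = Φ(0.713) = 76.2%

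The noncentral t calculation also gives 76.2%. The stated 76% therefore assumes a 5-year change from every one of the 3500 patients.

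**Step 2. Apply the plan's own graft survival.**
- AlloSure: 0.75 × 2500 = 1875
- Controls: 0.70 × 1000 = 700
- √(1/1875 + 1/700) = √0.001962 = 0.04429
- Z = 3 / (30 × 0.04429) = 2.258
- power = Φ(0.298) = 61.7%

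The noncentral t calculation again gives 61.7%. The loss is 76.2 − 61.7 = 14.5 percentage points.

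**Step 3. Express the gap in other terms.**
- Difference detectable with 76% power among 1875 and 700: 30 × 0.04429 × (1.960 + 0.706) = 3.54 mL/min, against 3.0 planned.
- Enrolment needed to keep 76% power for 3.0 among surviving grafts: about 1395 controls and 3488 AlloSure patients, about 4883 in total.

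**Step 4. Could the 76% already include lost grafts, scored as an eGFR of zero?** The article gives no baseline eGFR, so this needs an assumption. If lost grafts were scored zero and survivors did not change on average, the control mean decline would be 0.30 × baseline, which reaches 12 at a baseline of 12 / 0.30 = 40. For AlloSure, 9 / 0.25 = 36. At higher baselines the stated means would fit only if survivors improved on average. The article states no such scoring rule.

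**Step 5. Scale.** The 25% difference in the power statement is 3 / 12, a ratio of mean declines. It is not a percentage change from each patient's baseline, which is one way to read the endpoint definition in Outcomes and Measures.

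**The case against.** The strongest reply is that the article nowhere says patients with graft loss or death are excluded. It allows a nonparametric analog, and a rank test can keep everyone by giving losses the worst ranks. How deaths and lost grafts enter a secondary endpoint is commonly left to the analysis plan, which is not shown. **This stands.** The lost power and the selection problem apply to a survivors-only comparison and must be stated conditionally. It does not rescue the 76%, which was calculated from means and an SD for all 3500 patients and not for a worst-rank analysis. Nor does the inclusion rule under Statistical Analysis (at least one AlloSure assessment) help: it creates no 5-year eGFR for a lost graft.

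A reader might go further in four ways that the documents do not support.

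- **That the survivor comparison is biased by a known amount, toward too small a difference.** If 12 and 9 describe patients who have a 5-year value, then 3.0 already is the survivor difference. It shrinks only if those means are taken to cover lost grafts and deaths as well, and the article does not say which is meant. Nor are the losses shown to be mainly rapid decliners: the Introduction attributes 47% of losses after 10 years to death with a functioning graft.
- **That the 65% attrition rate cuts the eGFR sample further.** That figure is attached to the log-rank calculation and its meaning is unclear, so it is not used here.
- **That the two scales are a flat contradiction.** The phrase in Outcomes and Measures may simply mean the comparison between groups. It is loose wording that needs tidying.
- **That a slope model should replace the planned test.** Controls come from registry data, and repeated eGFR for them is not established. The quarterly window in the Discussion is described for laboratory values that accompany AlloSure draws.

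**Conclusion.** The point holds as a correction to a stated figure. On the plan's own inputs, 76% power requires a 5-year eGFR from every patient, while the adjacent paragraph expects about 1875 and 700 surviving grafts. A t test limited to these has about 62% power for the planned 3 mL/min.

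The 62% rests on three assumptions: the difference of 3 and the SD of 30 hold among survivors, graft survival is as planned, and every surviving graft has a recorded 5-year eGFR.

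Such a comparison is also open to selection bias, because it conditions on an outcome the intervention is expected to change. The documents fix neither the size nor the direction of that bias. Since this is a secondary endpoint and the remedy is mainly wording, it should be corrected but does not threaten the trial.

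**What to change.** 1. **Restate the power.** For a t test among surviving grafts, say that about 1875 AlloSure patients and 700 controls are expected to have a 5-year eGFR, giving about 62% power for a 3 mL/min per 1.73 m2 difference with SD 30, and 76% power for about 3.5.
2. **State how graft loss and death enter the comparison, and add an analysis that keeps everyone.** The nonparametric option already allowed can do this, with graft loss or death given the worst rank. Its power differs from both figures above and needs its own calculation if quoted.
3. **Use one scale.** Define the endpoint as absolute change in mL/min per 1.73 m2 in both Outcomes and Measures and the sample size text.
4. **Optional.** Add a slope model on repeated eGFR if registry controls prove to have the measurements.

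The cost is a less favourable stated power and a little more analysis work. The rank analysis needs only graft loss and death, already part of the primary endpoint, beyond the 5-year eGFR already planned.

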### Statistical Analysis

Data will be assessed for normalization and are likely to be nonparametric. Appropriate statistical tests will be applied with the final analysis occurring at the end of the study. Statistical assessments resulting in a *P* value <.05 will be deemed significant. All participants who have at least one AlloSure assessment during the surveillance period will be included in the analysis.

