**Methods:**

The study protocol will acquire data from a phase IV observational trial to assess a cohort of renal transplant patients managed using AlloSure dd-cfDNA and patient care managers versus 1000 propensity-matched historic controls using United Network for Organ Sharing U.S. Scientific Registry of Transplant Recipients data. Data will be managed in a centralized electronic data server. The primary outcome will be superior allograft survival, as a composite of return to dialysis, retransplant, death due to allograft failure, and death with a functional graft (infection, malignancy, and cardiovascular death). The secondary endpoints will assess improved kidney function through decline in estimated glomerular filtration rate and immune activity through development of donor-specific antibodies.

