### Testing Schedule

Patients will have quarterly AlloSure dd-cfDNA testing (every 3 months) as part of their posttransplant surveillance for a period of 5 years. DSA, eGFR, routine transplant bloods, and clinical events will be captured using the standard of care regime as per institutional guidelines (Figure 1).

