### Participants

All patients who underwent a kidney transplant within ≥6 months and ≤18 months will be screened to identify patients who are eligible for the study based on inclusion and exclusion criteria. Patients who are eligible to enter the study will be approached for consent during their routine posttransplant clinic visits and will be considered enrolled when they have signed the informed consent form. Selection criteria are shown in Textbox 1.

Study selection criteria.

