**Inclusion Criteria**
First draw for purposes of this study ≥6 months and ≤18 months from date of transplantKidney transplant recipient (retransplant and dual kidney permitted)Patient’s health care provider adopts and intends to apply the AlloSure Routine Testing Schedule (quarterly draws)Participant is willing and able to give informed consent for participation in the trialMale or female, aged 12 years or olderIn the investigator’s opinion, patient is able and willing to comply with all trial requirements

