By providing a surveillance tool like AlloSure and patient care management to community nephrologists via TRACK, we can allow a more comprehensive assessment of the patient and allograft beyond the traditional measures such as eGFR, creatinine, and DSA values. With TRACK, when a patient has transitioned to a community center, they will continue to have access to dd-cfDNA testing to monitor allograft status. Longitudinal surveillance of dd-cfDNA will provide an understanding of patient-specific baselines, which serve as a reference point to identify actionable changes in dd-cfDNA that may indicate significant clinical events requiring further investigations and intervention.

This study will also be conducted over a duration of 5 years postenrollment. While the 1-year survival of many kidney transplants is quite good, those further from transplant have worsening survival. This extended timeline is essential to understanding allograft survival, as there is a rapid decline in allograft failure after 3 years posttransplant. Therefore, the longer-term survival of those managed with AlloSure dd-cfDNA and close patient care management will be the primary aim of this study.

While a vast majority of clinical practice adheres to a standard schedule, transplantation is unique in that the timeframe and the testing modality schedule are specific to each transplant center. This heterogeneity is further divided once a patient transfers from the transplant center to the community practice. With this patient population, we acknowledge not every patient will be monitored for DSA or standard labs at the same intervals. The data capture system will be designed to accommodate a quarterly window for the labs that are available to correlate with the AlloSure dd-cfDNA draws.

The TRACK study will assess the validity of dd-cfDNA surveillance and patient care management in kidney transplant patients, aiming to demonstrate superior allograft survival, graft function, and immunological status. This will provide important insights into risk factors for poor clinical outcomes, detect molecular allograft injury and rejection, and identify opportunities for early intervention.

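### AlloSure participants enter the analysis only if a draw follows consent, so graft losses and deaths before that draw are dropped from one arm only

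*Protocol article*

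**What the plan says.** The Statistical Analysis section of the protocol article gives one rule for who is analysed: "All participants who have at least one AlloSure assessment during the surveillance period will be included in the analysis". A draw at any time in the surveillance period qualifies.

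Under Participants, eligible patients "will be considered enrolled when they have signed the informed consent form". The draw is a separate event: the inclusion criteria place the "First draw for purposes of this study" between 6 and 18 months after transplant.

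The primary endpoint is "superior graft survival measured as the time to allograft loss", a composite that includes death. No time origin is given with it. The Discussion says "This study will also be conducted over a duration of 5 years postenrollment", and Study Design likewise describes five years of enrolment per patient.

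The comparator is "1000 propensity-matched historic controls using United Network for Organ Sharing U.S. Scientific Registry of Transplant Recipients data". The sample-size paragraph counts 3500 patients, "of which 2500 will be periodically assessed with AlloSure and 1000 are matched controls receiving standard of care".

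**The concern.** Inclusion depends on something that happens after enrolment and that a patient must be event-free to reach. If the clock starts at consent, every analysed AlloSure participant is guaranteed to be event-free up to the first draw. Those who were not are deleted. This is immortal time, and it works in one direction: early primary-endpoint events leave the AlloSure arm, while nothing comparable leaves the control arm.

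Propensity matching on baseline covariates does not repair this, because the selection is on survival after enrolment. The comparison is non-randomised and uses historic controls, so no other feature of the design offsets it. The primary superiority claim is what is at stake.

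**Working it through.** **Inputs from the protocol article.** 2500 AlloSure and 1000 control patients; two-sided log-rank test at 5%; five-year graft survival 75% against 70%; hazard ratio 0.807; power 87%; first draw 6-18 months after transplant; quarterly testing.

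**The plan's own figure.** HR = ln(0.75)/ln(0.70) = 0.8066. Expected events = 1000 × 0.30 + 2500 × 0.25 = 925. Freedman's formula with allocation ratio 2.5 gives z = 0.1934 × √(2.5 × 925) / (1 + 2.5 × 0.8066) − 1.96 = 3.08 − 1.96 = 1.12, so power is 86.9%. The stated 87% is reproduced, without any attrition. The survival figures can therefore be used as the base.

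**Assumptions for the bias.** No true effect; constant hazard λ = −ln(0.70)/5 = 0.0713 per year in both arms; clock at consent; gap from consent to first draw uniform from 0 to g years; controls followed from a comparable start with no such condition.

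**Apparent AlloSure survival at five years.** A patient with gap u has survival exp(−λ(5 − u)). Averaging over u gives 0.70 × (exp(λg) − 1)/(λg):

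- g = 3 months: 70.6%
- g = 6 months: 71.3%
- g = 12 months: 72.6% (12 months is the widest gap the entry window allows)

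A check by counting for g = 3 months: of 2500 who consent, about 2500 × 0.0713 × 0.125 = 22 have an event before the draw and are removed. Of the remaining 2478, 750 − 22 = 728 have an event by five years, or 29.4%, which is again 70.6% survival.

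**False superiority.** Trials of 2500 against 1000 were simulated under these assumptions and tested by log-rank, with 1500 or 2000 trials per run. Results are the share significant in favour of AlloSure, against 2.5% nominal:

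| Gap from consent to first draw | False superiority |
|---|---|
| none | 2.0-3.4% |
| uniform 0-3 months | 6-7% |
| fixed 3 months | 14% |
| uniform 0-6 months | 14-16% |
| uniform 0-12 months | 42-43% |

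The ranges are the spread between separate runs.

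**A worst case that the article does not state.** If both arms were timed from transplant without delayed entry, with AlloSure entry uniform over 6-18 months, the guaranteed event-free time would be 0.5-1.5 years. The average of exp(−λ(5 − u)) over that range is 75.2% against 70%, with about 95% false superiority. The guaranteed time that turns 70% into exactly 75% is 5 + ln(0.75)/λ = 0.967 years, or 11.6 months. This result depends on the hazard shape. Keeping 70% at five years but letting a Weibull hazard rise, the 75.2% falls to 73.5% (shape 1.25), 72.3% (1.5) or 71.1% (2). The shapes are assumed.

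**The case against.** A reader might infer that the analysis-set rule alone could manufacture the planned 75% against 70%. The documents do not support that. The figure needs a clock at transplant, which is stated nowhere; the Study Design, sample-size and Discussion text points to an enrolment or surveillance clock. It would also come from the 6-18 month entry window, and would arise even if every consenting patient were analysed. A constant hazard enlarges it, and the Discussion describes good one-year survival that worsens later. If AlloSure patients were timed from enrolment and controls from transplant, the entry window would produce survivor selection rather than immortal time, and with a rising hazard that could even run against AlloSure.

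A reader might also infer that the rule, taken literally, excludes all controls. That reading is strained: participants in the selection criteria are people who consent, and the sample-size paragraph plainly counts 1000 controls.

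Further, quarterly testing, mobile draws and care-manager scheduling make a long gap after consent unlikely. The first draw is itself written into the inclusion criteria, so surveillance may be meant to start there, in which case there is no guaranteed time. The article condenses a fuller protocol, which may define the control index date. All of this stands, and it limits both size and confidence. The silence on a control index date is weak evidence by itself.

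What remains is a rule the article does state, beside an enrolment point and a follow-up period that it also states. Together they drop events in one arm. It could be said that starting at the first draw keeps the same patients in the analysis. It does, but with the clock starting there the period before the draw is no longer counted as follow-up, and the guaranteed event-free time disappears.

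**Conclusion.** The point holds in a limited form. Conditioning the AlloSure arm on a draw that can follow consent biases the primary comparison toward AlloSure when time runs from enrolment, as the article suggests. With first draws within one quarter, the bias is about 0.6 of the planned 5 percentage points (1.3 if every draw comes at exactly three months). False superiority is then about 6-7% (14% for the fixed gap) instead of 2.5%. It reaches 42-43% only if first draws are spread over a full year, which fits poorly with the planned testing support. These figures rest on no true effect, a constant hazard and, except for the fixed gap, a uniform gap; the article gives no distribution for the gap.

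This should be fixed, with moderate confidence, since the full protocol or SAP may already align the control start date.

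**What to change.** Start the AlloSure clock at the first study draw. Give each matched control an index date at the same time since transplant, require the control to be alive with a functioning graft on that date, and start its clock there. Replace the inclusion sentence in Statistical Analysis with wording such as: *The analysis includes all AlloSure patients from their first study draw, and all matched controls alive with a functioning graft at the corresponding index date.*

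As a sensitivity analysis, include everyone who consented, timed from consent whether or not a draw followed, with control index dates set to the matching time since transplant.

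The cost is protocol or SAP wording and an index-date step when controls are extracted from the registry. No new data are needed, and the change should be made before extraction.
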